### Sweat test

A small electrical current is applied to the forearm, following which a collecting device is used to collect up to 0.5ml of sweat over a 20 - 30-minute period. This is done on both forearms in parallel. The sample will be sent and processed by our local laboratory.

### Blood tests

Venepuncture equipment will be used to take up to 20mls of venous blood. Clinical samples will be sent to the local laboratory for analysis for full blood count, liver function tests (ALT, ALP, AST, Gamma-GT, total bilirubin, and albumin), vitamin profile (vitamins A, D and E), renal function (urea, creatinine, eGFR, potassium and sodium). Tests will be analysed as per local lab procedures.

One sample will be designated for CFTRm assay validation and storage (a serum sample (ca. 200 microliters if singlicate) for qualitative and quantitative analysis of CFTRm and their major metabolites using LC-HRMS or LC-MS/MS).

A further sample will be for micronutrient analysis, PAPP-A and hormonal e.g. β-hCG analysis – this will be run as batches.

### Breastmilk sample

Participants will be asked to express up to 5ml of breastmilk which can be done at home or in a clinical setting at their preference. These will then be stored and used for validation of CFTRm assay.

### Qualitative Interviews

Qualitative interviews would take place via MS Teams with a member of the research team and would be recorded and transcribed using MS Teams software. We will make it clear to participants that they can decline to answer specific questions or end the interview should they choose to do so. If it is clear to the interviewer that a participant finds particular questions or themes distressing, we will remind them that they can stop at any time. We would anticipate the interviews taking between 30-60 minutes.

### Spirometry

This is usually performed during or prior to scheduled clinic visits using a handheld home spirometry device as part of standard care. The results are visible through the linked online application. Additional laboratory spirometry would not be required.

### Sputum samples

If the participant is able to produce a sputum sample this would be taken and processed for microbiology as per the clinical microbiology SOP. If unable to produce a sputum sample, then a cough swab or induced sputum (if not pregnant) would be an acceptable alternative (both regular clinical practice). Excess sputum not required for clinical evaluation would be stored and saved for potential further research analysis.

### Urine sample

Participants would be able to bring this sample from home in a universal container. The first urine of the day is preferred but this is not essential. A minimum volume of 5ml would be required.

### CT scan

A lung CT scan will take place in the first visit pre-conception with a second CT scan planned for 6-12 months post-partum if not breast feeding.

### Oxygen-enhanced Magnetic Resonance Imaging (OE-MRI) of lungs

Up to three oxygen enhanced lung MRIs are proposed:

- 1. prior to conception,
  2. during the third trimester, and
  3. six-months post-partum.

These MRIs will focus on the adult participant’s lungs to assess for any structural or functional changes.

Before the MRI is carried out, the study team will confirm that the participant does not have any contraindications to MRI using the local MRI safety checklist. If the participant is unable to tolerate the MRI for any reason, the procedure will not go ahead. Sedation is not an option for this study.

Headphones will be provided to support increased comfort in the scanning machine. All scans will be performed lying supine, but for the scan in the third trimester this will be a ‘supported supine’ position using pillow/wedges to adjust positioning and improve comfort.

The scan will take 20 – 40 minutes and will involve a short period of breathing 100% oxygen via a facemask. The study team is very experienced in performing oxygen enhanced lung MRI in adults and children and the broader research team has previously performed oxygen enhanced placental imaging via MRI during pregnancy. If any abnormalities are detected on the scan, they will be discussed with the clinical team. Participants will be consented about the risk of false positive or incidental findings. There is no associated radiation risk with MRI, and it can be safely performed in pregnancy.

### Fetal MRI

The fetal MRI will be undertaken at the same time as the maternal third trimester scan. The maternal images will be obtained first with fetal imaging obtained immediately after. There will be a focus on imaging the fetal eyes for lens opacities, and the lung for any changes in lung development. This will add a further 10 - 20 minutes to the MRI time. Depending on emerging research, images obtained may later be processed to review other areas of anatomy, development and function. Consent forms will include this option.

### Questionnaires

The questionnaires being used are validated study questionnaires, and some are therefore subject to copyright restrictions in terms of the forms distributed to participants. Some have a section for participant’s name. The original questionnaires will be kept in the patient’s medical notes as they have clinic relevance. The results will then be transcribed and stored anonymously on the research database under the participants research identifier.

## ‘Mini’ and ‘Midi’ sub-study assessments

### Summary flow chart of study assessments (Table 2 & 3)

‘Mini’ Sub-Study (Table 2)

A phone or video call will take place before the first in-person visit to review inclusion/exclusion criteria and will be repeated in person at the first visit.

There are no strict time-windows in which each visit must be completed, but preferably they should be as close as possible to the designated visit. If a participant is enrolled at an older age than 8 weeks (for example any age up to 12 months), all the procedures from Visit 1 should still take place at the first visit, with the schedule then proceeding as below.

| Study Procedure | Visit 1  4-8 weeks age | Visit 2  6 months of age | Visit 3  12 months of age | Visit 4  24 months of age |
| --- | --- | --- | --- | --- |
| **For all children enrolled** | | | | |
| Informed consent | X |  |  |  |
| Inclusion/exclusion criteria | X |  |  |  |
| Demographics | X |  |  |  |
| Baseline assessments^1^ | X |  |  |  |
| Medical History^2^ | X | X | X | X |
| Physical examination^3^ | X | X | X | X |
| Liver function blood tests^4^ | X | X | X^5^ | X^5^ |
| Sweat test^6^ | X | X^7^ |  |  |
| Faecal elastase^8^ | X | X^7^ |  |  |
| Cranial ultrasound^9^ | X |  |  |  |
| **Only for children exposed to CFTRm** | | | | |
| Document ophthalmological review^10^ | X |  | X^5^ | X^5^ |
| CFTRm assay^11^ | X | X | X^5^ | X^5^ |
| **Key**:  X: Planned completion date  Highlighted in grey: tests that are additional to standards of practice. Note that all tests for children not exposed to CFTRm are additional to standards of practice.  1. See section 9.4.2  2. See section 9.4.4.  3. See section 9.4.5.  4. See section 9.4.6  5. Only if breastfed and exposed to CFTR modulator in last 6 months  6. See section 9.4.8  7. If exposed to CFTRm via breast feeding at the 4 – 8 weeks visit to repeat at 6 months. If still exposed at 6 months repeat at 12 months and so on, as exposure to CFTRm via lactation could affect results  8. See section 9.4.9.  9. See section 9.4.10  10. See section 9.4.3  11. See section 9.4.7 | | | | |

‘Midi’ Sub-study (Table 3)

As for ‘Mini’, a phone or video call will take place before the first in-person visit to review inclusion/exclusion criteria and will be repeated in person at the first visit.

All tests for all participants in the ‘Midi’ study are additional to standards of practice.

| Study Procedure | Age 3 - <5 years at time of recruitment | | Age 5+ at time of recruitment |
| --- | --- | --- | --- |
|  | First visit | Second visit (once aged 5+) | Single visit |
| Informed consent | X |  | X |
| Inclusion/exclusion criteria | X |  | X |
| Demographics | X |  | X |
| Baseline assessments^1^ | X |  | X |
| Medical history^2^ | X | X | X |
| Physical examination^3^ | X | X | X |
| Sweat test^4^ | X |  | X |
| O2 enhanced Lung MRI^5^ |  | X | X |
| Lung clearance index^6^ | X | X | X |
| **Key**:  X: Planned completion date  1. See section 9.4.2  2. See section 9.4.4.  3. See section 9.4.5.  4. See section 9.4.8  5. See section 9.4.12  6. See section 9.4.11 | | | |

### Review of medical records (baseline assessment)

The review of the child’s and parental medical records as listed below should be completed using a combination of parental reporting and medical records.

For all participants the below information should be recorded:

- Gestation in weeks, singleton/multiple birth, mode of delivery, APGAR score (at 1/5/10 min), admission to SCBU/NICU (Yes/No, and indication)
- Newborn blood spot: immunoreactive trypsinogen (IRT) result
- Birth weight in kilogram and centile, head circumference in centimetres and centile.
- NIPE outcome (normal/abnormal; specify abnormality)
- 6-week GP examination result
- Maternal health:
  - - Age, comorbidities, medications, ante/perinatal complications
- Parental genetics (to be accessed via relevant medical notes after informed consent obtained from each parent):
  - CF genotype of parent with known diagnosis
  - CF genetic screening result of non-CF parent if performed.

For participants exposed to CFTRm during pregnancy and or via lactation, to document:

- CFTR genetics results
  - - Would only have been carried out if mother has CF and male partner is either a known carrier, has unknown CFTR genotype, or had only undergone a common variant screen.

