## Primary Objectives

1. **Sub-study ‘Mama’**
   1. To record the obstetric and neonatal outcomes of females with CF.
   2. To record CF-related health outcomes among females with CF including pulmonary (e.g. ppFEV_1_) and nutritional status (e.g. BMI) during pregnancy and early parenthood (up to 24 months).
   3. To record the subjective experiences of family planning, pregnancy and early parenthood in females with CF.
   4. To describe the impact of diabetes (pre-existing and gestational) on obstetric, neonatal and CF related outcomes.
   5. To record sweat chloride results during pregnancy and/or lactation among females with CF in relation to CFTR modulator therapy.
2. **Sub-studies ‘Mini’ and ‘Midi’**
   1. To collate clinically obtained serum liver enzymes levels and to record the frequency of congenital abnormalities (including ophthalmic cataract screening), in children born to a parent with CF (females or males with CF).
   2. To document cases of ‘missed’ CF-diagnoses due to false negative immunoreactive trypsinogen (IRT) results in children of females with CF in relation to transplacental and/or lactational exposure to CFTR modulators.
   3. To record lung function using lung clearance index (LCI) for young children (aged three-to-six years) born to a parent with CF.

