## Endpoints

### Primary endpoints

As an observational study, a combination of multiple endpoints will be monitored to identify areas of interest that may warrant and benefit from future investigation in larger studies.

Below are the endpoints which will be explored based on the currently available literature and research in the field.

*‘Mama’ sub-study*

1. Change in percent predicted FEV_1_ (ppFEV_1_) from pre-conception/baseline to end of pregnancy, and at 12- and 24-months post-partum.
2. Incidence of CF-related pulmonary complications during pregnancy.
3. Incidence of premature delivery (defined as birth <37 weeks gestation).

*Combined ‘Mini’ and ‘Midi’ sub-study*

1. The number of participants with:
2. Liver dysfunction (ALT/AST/GGT/bilirubin above upper limit of normal). This is prospectively obtained in the ‘Mini’ sub-study, and retrospectively reviewed from medical records in the ‘Midi’ sub-study.
3. Presence of congenital abnormalities including cataracts (based on medical history and examination)
4. The number of participants with normal IRT subsequently diagnosed with CF (based on a combination of CF genetic tests, sweat chloride, and faecal elastase where appropriate)
5. The number of participants with an abnormal lung clearance index (LCI) (‘Midi’ only)

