### Primary endpoint analysis

A descriptive analysis of the endpoints will be completed. For categorical variables (e.g. presence of cataracts) they will be summarised as frequencies (%). For continuous variables (e.g. weight centiles) they will be reported as a mean (standard deviation) or median (inter-quartile ranges) dependent on sample distribution.

For comparisons across CFTRm exposed and non-exposed groups, a chi-square or Fisher’s exact test will be used for categorical variables, and a two-sample t-test or Mann-Whitney U test for continuous variables. Confounders including but not limited to cumulative time of exposure to CFTRm, maternal health, and gestation of offspring will be considered.

In the ‘Mini’ sub-study, enrolling offspring for their first visit up to the age of 12 months allows for maximising sample size although resulting in the possibility of missing early life events. A sensitivity analysis to test assumptions such as only including those up to six months of age will be undertaken.

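### The missed-CF primary endpoint is not ascertained alike in CFTRm-exposed and non-exposed children: the child's CFTR genetics is listed for recording only if exposed, and the direction of any bias is uncertain

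*Protocol*

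**What the plan says.** Protocol section 15.2.1 gives as a combined 'Mini' and 'Midi' primary endpoint the number with "normal IRT subsequently diagnosed with CF (based on a combination of CF genetic tests, sweat chloride, and faecal elastase where appropriate". The objective behind it (section 5.2, second objective for 'Mini' and 'Midi') is to document missed diagnoses "in children of females with CF in relation to transplacental and/or lactational exposure to CFTR modulators".

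Section 9.4.2 sets out what is taken from the records. For every child this includes the IRT result, the genotype of the parent with CF and any genetic screen of the other parent. The child's own CFTR genetics is in a separate list, headed "For participants exposed to CFTRm during pregnancy and or via lactation, to document". The note beneath it explains who will have been tested: "Would only have been carried out if mother has CF and male partner is either a known carrier, has unknown CFTR genotype", or had only a common-variant screen.

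Table 2 (section 9.4.1) schedules one sweat test and one faecal elastase at visit 1 for every 'Mini' infant. Footnote 7 adds repeats: "If exposed to CFTRm via breast feeding at the 4 – 8 weeks visit to repeat at 6 months", then again at later visits while exposure continues. The reason given is that CFTRm in breast milk might alter the results. Table 3 gives every 'Midi' child one sweat test and has no elastase row.

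Section 15.4.2, on the primary endpoints, states: "For comparisons across CFTRm exposed and non-exposed groups, a chi-square or Fisher’s exact test will be used for categorical variables". It mentions confounders and a sensitivity analysis on age at entry. It does not mention that diagnostic testing differs by exposure.

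**The concern.** A count of diagnosed cases depends on how hard one looks as well as on how many cases exist. Here one named component of the endpoint, the child's genetics, is listed for recording in one comparison group only. A second component, the repeated sweat and elastase tests, is triggered by the exposure under study. The trigger for genetic testing in section 9.4.2 concerns the mother's CF and what is known of her partner's genotype. A non-exposed child of a mother with CF can meet it equally well, yet a result for that child has no listed place.

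The protocol's own clinical background (section 4.2.2) shows why genetics matters. It describes an ETI-exposed infant with CF whose IRT was below the threshold. CFTR testing, requested because the father was a known carrier, gave the diagnosis. Elastase was normal, and sweat chloride (60 and 67 mmol/L) was lower than expected during breast feeding.

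If the groups are compared as planned, a difference between them, or the absence of one, could come from the work-up and not from CFTRm.

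**Working it through.** The protocol gives no expected count, power or effect size for this endpoint, so there is no stated figure to reproduce. The check has three parts.

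**1. Diagnostic information by group (section 9.4.2, Tables 2 and 3)**

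| Group | Sweat | Elastase | Child's genetics listed for recording |
|---|---|---|---|
| 'Mini', non-exposed | 1 | 1 | No |
| 'Mini', exposed in utero only | 1 | 1 | Yes, where done |
| 'Mini', lactation-exposed | 2, up to 4 if exposure continues | same as sweat | Yes, where done |
| 'Midi', non-exposed | 1 | 0 | No |
| 'Midi', exposed | 1 | 0 | Yes, where done |

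The genetics difference runs through both sub-studies. The repeat-test difference is confined to lactation-exposed 'Mini' infants.

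**2. Effect on an observed ratio (illustration, all sensitivities assumed)**

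Take the same true missed-CF risk in both groups. Let s be the chance that an undistorted sweat/elastase round detects CF (0.70 to 0.98), sm the chance while CFTRm distorts it (0.30 up to s), and g the share of exposed cases with a genetics result (0 to 1). Rounds are taken as independent, and a non-exposed child's genetics as not counted.

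- Non-exposed: d0 = s.
- Exposed in utero only: d1 = 1 − (1 − g)(1 − sm).
- Lactation-exposed, with one repeat after exposure has ended: d1 = 1 − (1 − g)(1 − sm)(1 − s).

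The ratio d1/d0 at selected values:

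- In utero only, s = 0.98, sm = 0.30, g = 0: 0.30/0.98 = 0.31.
- In utero only, s = 0.70, g = 1: 1/0.70 = 1.43.
- Lactation, s = 0.98, sm = 0.30, g = 0: (1 − 0.70 × 0.02)/0.98 = 0.986/0.98 = 1.01.
- Lactation, s = 0.70, g = 1: 1/0.70 = 1.43.

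Across the grid the ratio is 0.31 to 1.43 for in-utero-only exposure and 1.01 to 1.43 for lactation exposure. The second range stays above 1 only because the repeat is assumed undistorted. If exposure continues through both rounds, with s = 0.90, sm = 0.30 and g = 0, detection is 1 − 0.70² = 0.51 and the ratio is 0.51/0.90 = 0.57.

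**3. Number of cases**

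Section 15.3.2 expects 25 to 35 'Mini' and about 20 'Midi' participants, so 45 to 55. This is an upper figure: some children may enter both sub-studies, and some have a father, not a mother, with CF. Assume that 2 to 10% of partners are carriers; half the children of a mother with CF and a carrier are affected.

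- Low: 45 × 0.02 × 0.5 = 0.45 cases; chance of at least one = 1 − 0.99^45 = 0.36.
- High: 55 × 0.10 × 0.5 = 2.75 cases; chance of at least one = 1 − 0.95^55 = 0.94.

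These are CF cases with any IRT result, so missed cases would be no more numerous.

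**The case against.** The strongest reply is that the study is descriptive. The objective is to document cases, the sentence on group comparisons is generic and does not name this endpoint, and a statistical analysis plan is to follow. The repeats have a sound purpose, since they offset distortion by CFTRm. A non-exposed child's CF diagnosis would still count under section 15.2.1, and history suggestive of CF is taken for every child at every visit (section 9.4.4).

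Much of this stands, and it rules out several stronger readings that a reader might infer:

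- That bias must run towards blaming CFTRm. Masking of sweat and elastase works the other way, and only some exposed children will have been genotyped.
- That the contrast is four test pairs against one. Four is a maximum for infants still exposed at later visits. Infants exposed only in utero follow the non-exposed schedule, and 'Midi' testing does not differ.
- That one case would decide the comparison. With one case in total, lying in an exposed group at least half the sample, Fisher's two-sided p is 1.
- That genetic diagnoses in non-exposed children are lost altogether. What is missing is a listed item. How many such results exist is unknown, and the CRF itself is not at hand.

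The reply does not remove the mismatch. The comparison sits under the primary endpoint analysis, and this is a categorical primary endpoint whose objective is framed in relation to exposure. Sections 13.3 and 15.1 place the analysis plan before final analysis, by which time an item left out of collection would have to be retrieved retrospectively.

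**Conclusion.** The point holds as one of unequal ascertainment with uncertain direction. Followed as written, section 9.4.2 leaves one component of a primary endpoint unlisted for the non-exposed group, for a reason that does not follow from the protocol's own trigger for testing. Footnote 7 adds a second difference in part of 'Mini'. An exposed v non-exposed test of this count would not be interpretable without knowing who had which test.

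The size cannot be fixed from the protocol. The ratios of 0.31 to 1.43 and 1.01 to 1.43 rest entirely on assumed sensitivities, and the 0.45 to 2.75 cases on an assumed carrier rate. They show that distortion in either direction is possible and that a formal test has very little to work with. They do not show that any particular bias will occur.

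**What to change.** - In section 9.4.2, move the child's CFTR genetics result, with the reason for testing, to the list recorded for all participants, where a result is available.
- Report by exposure group which diagnostic tests each child completed and how each case was found.
- Restrict the missed-CF count to children of females with CF, as the objective states, with a normal IRT. Split it by the non-CF parent's status (known carrier, untested, screened negative), using the parental screening result already recorded for all.
- Report the endpoint descriptively, counting cases found by any route, without a formal exposed v non-exposed test. If a comparison is wanted, apply one common case definition that uses sweat and elastase results obtained after lactational exposure has ended, and say how 'Midi' children, who have no elastase, are handled.
- Do not limit the comparison to first tests. In lactation-exposed infants those are the results footnote 7 says may be affected, and a case like the one in section 4.2.2, found by genetics, would drop out of the count.

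No new test is needed. The cost is one more CRF line for non-exposed children, some wording in section 15.4.2 and, under the descriptive option, no p-value for this endpoint.

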### Documentation of ophthalmology review

For children exposed to CFTRm in utero or via lactation they will be referred to ophthalmology as per local standards of care. This review is to rule out lens opacities (cataracts). This ideally should happen in the first two months of life if *in utero* exposure and then yearly while exposed to CFTRm via breast feeding. Parents should be asked to bring the letter of the review to then document whether cataracts were observed or not.

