### Clinical data

Existing studies of females with CF showed a degree of subfertility (15) when compared to the general population, thought to be multifactorial. Those females with CF who did get pregnant were found overall to have an increased rate of premature birth, lower birth weight infants, and higher risk of obstetric complications such as gestational diabetes (16). Significant bacterial pathogens were also implicated in the poorer longer-term outcomes, with a case series showing that three out of four women who died shortly following pregnancy were chronically infected with *Burkholderia cenocepacia* (18).

More recent studies have also looked at the implications of continuing/ceasing CFTRm in pregnancy. This has shown that those women who do stop will often restart due to significant deterioration in their own physical health (19)(5). Further studies have also shown that whilst the ante-partum period does not confer significant health risks, the first year of parenthood has resulted in increased risk of pulmonary exacerbations and overall health decline (20).

Whilst there are no known definitive side effects of CFTRm in infants exposed in utero, it is already recommended that those children with CF who are treated with ivacaftor or an ivacaftor containing compound should have yearly ophthalmology screening in case of cataract formation (11). It is unknown if in utero or lactation exposure to infants is equivalent to these directly administered therapeutic doses but raises questions already being explored.

Jain et al. (21) reported a case series in which 3 of 23 human infants born to mothers with CF taking ETI during pregnancy were diagnosed with bilateral congenital cataracts. The infants did not have any alternative explanation or risk factors for cataract formation. However, these cataracts were small, considered visually insignificant and were detected not on routine newborn eye checks using the red reflex, but at specialist paediatric ophthalmoscopy screening. The frequency of such subclinical changes in the general population is unknown. The current median prevalence of childhood cataract in the general population is 1 per 10,000 (22) with the sample size currently too small to make a comparison in an ETI exposed group.

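### Specialist cataract review is arranged only for CFTRm-exposed infants, so the planned exposed versus non-exposed comparison cannot separate an excess of cataract from better detection

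*Protocol*

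**What the plan says.** Protocol section 9.4.3 limits the eye referral by exposure: "For children exposed to CFTRm in utero or via lactation they will be referred to ophthalmology as per local standards of care". Table 2 in 9.4.1 agrees. It lists the documented ophthalmology review in the block headed "Only for children exposed to CFTRm", and its footnote restricts the 12- and 24-month reviews to children breastfed and exposed in the preceding six months.

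Section 15.2.1 makes this a primary endpoint for the combined Mini and Midi sub-studies: "Presence of congenital abnormalities including cataracts (based on medical history and examination" is counted in all participants. Section 15.4.2 uses cataract as its example of a categorical endpoint: "For categorical variables (e.g. presence of cataracts) they will be summarised as frequencies". The next paragraph begins "For comparisons across CFTRm exposed and non-exposed groups" and plans a chi-square or Fisher's exact test for categorical variables. It makes no exception for cataract.

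The background in 4.2.2 describes a case series in which 3 of 23 infants had small bilateral cataracts that "were detected not on routine newborn eye checks using the red reflex, but at specialist paediatric ophthalmoscopy screening". It adds: "The frequency of such subclinical changes in the general population is unknown".

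**The concern.** The method that finds the outcome is applied to one comparison group and not to the other, and exposure itself decides which group gets it. By the protocol's own account, the checks that non-exposed children do have missed the opacities of concern. For those opacities the observed rate would be higher in exposed children even if CFTRm had no effect on the lens.

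Cataract is one of the safety questions that motivate the infant sub-studies. The results are meant to support monitoring guidelines (4.3) and to help power later studies (15.3.1). A difference in reported frequencies that partly or wholly reflects who was examined would carry through to both.

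**Working it through.** The plan states no rate, sample size or power for this comparison, so there is no figure to reproduce. The check has two parts.

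**1. Who is examined, and how**

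| Source of eye findings | Exposed | Non-exposed |
|---|---|---|
| Newborn examination and 6-week GP check (9.4.2) | recorded | recorded |
| Study general examination (9.4.5; names no eye examination) | yes | yes |
| Optional third-trimester fetal MRI, Mama pregnancies only (9.3.13) | some | some |
| Specialist ophthalmology review in Mini (9.4.1 Table 2, 9.4.3) | yes, repeated while exposure through breastfeeding continues | no |
| Eye assessment in Midi (9.4.1 Table 3) | none scheduled | none scheduled |

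The unequal detection therefore arises from the Mini schedule. Section 15.4.2 does not correct it: "Confounders including but not limited to cumulative time of exposure to CFTRm, maternal health, and gestation of offspring will be considered". Method of ascertainment is not named. Adjusting for the listed factors could not remove the problem, because scheduled specialist review coincides with exposure and leaves no overlap between the groups. Within the exposed group, longer breastfeeding exposure also brings more eye reviews, so an analysis by duration of exposure is biased in the same direction.

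**2. Size of the artefact with no true effect**

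Inputs:
- True rate p, the same in both groups: 3/23 = 13.0% from 4.2.2, exact (Clopper-Pearson) 95% CI 2.8% to 33.6%. Using a case series as a prevalence is an assumption.
- Detection with specialist review, d_E = 1 (assumed).
- Detection without it, d_U = 0 to 0.25 (assumed).
- Mini total: 25 to 35 infants (15.3.2).
- Exposed share: not stated; 50% to 90% assumed. Section 4.1 puts continuation of CFTRm in pregnancy at about 90%, and offspring of fathers with CF are also enrolled.

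Observed rate = p × d, so the artefactual difference is p × (d_E − d_U).

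- Exposed: 13.0% × 1 = 13.0%.
- Non-exposed: 13.0% × 0 = 0%, up to 13.0% × 0.25 = 3.3%.
- Difference: 9.8 to 13.0 percentage points.
- At p = 3%: 3% × 0.75 = 2.25 points, up to 3 points.
- At p = 33.6%: 33.6% × 0.75 = 25.2 points, up to 33.6 points.

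Example at p = 13.0% with 35 infants, 24 exposed and 11 not: about 24 × 0.130 = 3.1 exposed cases are expected. The non-exposed have about 11 × 0.130 = 1.4 opacities, of which 0 to 0.36 are recorded. The chance of a numerically higher exposed rate is 97% with d_U = 0 and 84% with d_U = 0.25, against 48% with equal detection. Across the assumed sizes and shares it is 79% to 99%, against 42% to 65% with equal detection.

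Exact enumeration of Fisher's test (two-sided 0.05, assumed) gives a significant exposed excess from the artefact alone in 0% to 7.5% of cases at p = 13.0%. At p = 33.6% with near-equal groups it is 28% to 61% with 25 infants and 35% to 78% with 35, the upper figures being for d_U = 0.

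**The case against.** A reader might infer three stronger things that the documents do not support.

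The first is that any excess will be an artefact. That does not follow, because a true effect could be present alongside the bias. The documents support only that the two could not be told apart.

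The second is that cataract cannot be found in non-exposed children. They have newborn and 6-week checks, a general examination and, in some cases, fetal MRI directed at the lens, so larger cataracts may be found in either group. The argument holds for the small opacities described in 4.2.2.

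The third is that the test will produce a false positive. At 13% it rarely would. Raw case counts would also exaggerate the problem: with only 5 non-exposed children, full detection would still give no cases with probability (20/23)^5 = 0.50. Rates are the right scale.

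It can also be said that the comparison sentence in 15.4.2 does not itself name cataract, that the study is descriptive and meant to flag areas for larger work, and that an analysis plan is still to be written. These points lower the severity. They do not remove the point: cataract is part of a primary endpoint, it is that section's own example of a categorical variable, nothing excludes it from the comparison, and this protocol already fixes both the unequal schedule and the comparison.

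**Conclusion.** The point holds in this form: for the subtle opacities described in 4.2.2, the exposed versus non-exposed comparison is biased towards an exposed excess, and an observed excess could not be distinguished from a detection artefact. With no true effect and a common rate of 13%, expected observed rates are 13% against 0% to 3.3%. That rests on the assumed common rate, full detection at specialist review and 0% to 25% detection elsewhere. The harm is mainly in the reported frequencies. A significant test from detection alone is unlikely at that rate with 25 to 35 infants, though not at the upper confidence limit with near-equal groups. This should be fixed, but it does not undermine the study as a whole.

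**What to change.** - In 15.2.1, list cataract or lens opacity separately from other congenital abnormalities.
- In 15.4.2, report ophthalmologist-detected opacities as n/N with an exact 95% CI, where N is the exposed children actually reviewed, and make no test against the non-exposed. The denominator matters because assessments are optional (6.1) and the result depends on parents bringing the review letter (9.4.3).
- Limit any between-group comparison of eye or congenital findings to sources recorded for all children: the newborn examination, the 6-week GP examination where available, and the study general examination, noting that 9.4.5 names no eye examination.
- State that Midi schedules no eye assessment.
- Reconcile the objective in 5.2, which reads as if cataract screening covered the offspring of mothers and fathers with CF alike, with Table 2, 9.4.3, 15.2.1 and 15.4.2.

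The cost is wording and one between-group p-value that could not be interpreted. No examinations are added and clinical care does not change.
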